## Methods/Design

### Study Design and Setting

This quasi-experimental study is being conducted in GCN services in the state of NSW, Australia. Within Australia, GCNs can be either registered or enrolled nurses who perform a diversity of roles depending on the service in which they work. The role has traditionally focused on providing a range of nursing care in people's homes such as assisting with activities of daily living, wound management, chronic disease care, continence management, palliative care, medication management, disability and dementia care. Coordination of care with other service providers and health promotion has also traditionally been a major part of their role.

A quasi-experimental design was chosen because it was not feasible to randomise the intervention according to individual patient or practitioners within the services. GCN services have been randomly allocated to an 'early intervention' group or 'late intervention' (comparison) group. 'Early intervention' services are provided with training and support for nurses in identifying and offering brief SNAP intervention for clients during routine consultations (see service-level intervention). Data is being collected from clients in both groups at baseline, three months and six months to examine short and medium term change in SNAP risk factors. This will enable a comparison of client outcomes between early and late intervention groups. After the six month data collection point the 'late intervention' group will be offered the same training and support as the early intervention group.

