### Power and Sample Size Calculation

The sample size calculation is based on the primary outcomes of change in continuous self reported measures of lifestyle risk factors rather than differences in proportion of individuals in each risk category (secondary outcomes). There is evidence that risk associated with diet, physical activity and weight is continuous [20-22]. Achieving a shift in risk categories is more difficult to demonstrate in the context of a brief intervention and would require a very large sample size which is beyond the scope and resources of this trial. Hence the focus is on change in continuous measures of lifestyle risk factors as the primary outcomes.

A sample size of 360 clients in each group (total n = 720) is required to have 80% of power to detect the following difference between intervention and comparison groups:

▪ Mean difference of 1 serve of fruit and vegetables consumed (equivalent to 22% increase in the 'early intervention' group);

▪ Mean difference of 1.2 for physical activity scores as measured by a validated brief physical activity assessment tool [23] (equivalent to a 29% increase in mean scores in the 'early intervention' group);

▪ Mean difference of 0.6 for alcohol risk scores as measured by the AUDIT-C tool [24] (equivalent to a 10% reduction in mean scores in the 'early intervention' group);

▪ Mean difference of 4.1 kg in self reported weight (equivalent to a 4.4% weight reduction in the 'early intervention' group).

This is based on 5% significance level and 80% power (β = 0.8 and α = 0.05) allowing 20% lost to follow-up and a design effect of 1.8 due to clustering. The expected differences between intervention and comparison groups has been estimated based on previous research [25]. These differences are also considered meaningful from a population health perspective. Baseline prevalence of risk factors is based on NSW Health Survey 2006 for individuals aged 45-74 years [26].

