### Late Intervention (comparison) group

Two of the four GCN services have been randomly allocated to the 'late intervention' condition. These services will not receive the study intervention till after the six month data collection point and continue to deliver 'usual care'. This will enable the effectiveness of the service and client level intervention to be assessed in comparison to usual practice.

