### Statistical Analysis

#### Client Outcomes

Change in clients' lifestyle risk factors between early intervention and late (comparison) services will be assessed using multilevel models. Because this is a quasi-experimental study, clients in the intervention group are not randomly allocated and may have characteristics that are related to outcomes independent of the intervention [39]. Co-variates will be included in the analysis to adjust for baseline differences between the intervention and control groups [40]. Regression method for clustered data or multilevel models will be used to adjust for confounding client variables such as age, gender, locality (rural versus urban), socio-economic status, existing health conditions and number of contacts with the nurse. Thus, this method is used to estimate intervention effect after adjustment for client characteristics [41].

In the study we will use multilevel models in which three repeated measures (the level 1 units) are nested within clients (level 2 units) [42]. Multilevel models can accommodate unbalanced data due to attrition or missing values. Linear multilevel models would be used for continuous response variables and multilevel logistic models used for binary responses. The independent variables will be intervention (1 = intervention & 0 = control), time (0 = baseline, 1 = three months & 2 = six months) as a continuous variable, sex, age, health status of the client and the interaction between intervention and time. This model will allow us to test for a significant interaction between time and intervention, which would indicate an effect of the intervention on outcomes [40,43].

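### The client outcome model has no term for the randomised service, so its test of intervention by time understates uncertainty: about 14% type I error at a nominal 5% if the protocol's own design effect applies to change

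*Protocol article*

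**What the plan says.** - **Unit of allocation.** Under Study Design and Setting, the protocol explains that "it was not feasible to randomise the intervention according to individual patient or practitioners within the services", and that "GCN services have been randomly allocated to an 'early intervention' group or 'late intervention' (comparison) group". The section on the comparison group gives the numbers: "Two of the four GCN services have been randomly allocated to the 'late intervention' condition".
- **Sample size.** Power and Sample Size Calculation asks for 360 clients per group at 5% significance and 80% power, "allowing 20% lost to follow-up and a design effect of 1.8 due to clustering".
- **Client model.** Statistical Analysis, Client Outcomes, sets the levels: "In the study we will use multilevel models in which three repeated measures (the level 1 units) are nested within clients (level 2 units"). The listed terms are intervention, time coded 0, 1, 2 "as a continuous variable, sex, age, health status of the client and the interaction between intervention and time".
- **Decisive test.** "This model will allow us to test for a significant interaction between time and intervention", and a significant interaction is to be read as an intervention effect.
- **Other wording on clustering.** The preceding paragraph of Client Outcomes mentions regression for clustered data or multilevel models, as a way to adjust for client confounders. It names no cluster. Under Nurse Outcomes, nurse scores are to be assessed for clustering.

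**The concern.** The design section and the sample size both recognise that clients come in services. The model that tests the effect does not. A client-level random effect handles the correlation among one person's three measurements. It does nothing for the correlation in change among different clients of the same service.

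Because the test is intervention by time, a service that is simply better or worse throughout does little harm: that difference largely cancels. What remains is service-to-service variation in change over six months. Such variation is plausible here. The protocol describes service-specific assessment forms, local referral directories, a seconded nurse at each early site, and nurses' own judgement on whether to intervene. With two services per arm, this variation averages out very little, yet the model's standard error does not include it.

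At stake is a false claim of effectiveness on client outcomes, including the primary ones, in a trial meant to inform nursing practice and policy.

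**Working it through.** **Inputs from the protocol.** Four services, two per arm; 180 clients recruited per service; 20% loss; design effect (DE) 1.8; alpha 0.05 (taken as two-sided, since sidedness is not stated); power 80%. No standard deviation and no ICC are given.

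**The plan's own figures.** 4 × 180 = 720; 720 × 0.80 = 576, or 288 per group and 144 per service. These agree with the protocol. The 360 per group cannot be rebuilt without a standard deviation. Solved backwards: 288 / 1.8 = 160 effective clients per group, which detects a standardised difference of (1.960 + 0.842) × √(2/160) = 0.313 with 80% power. This value is used below as the planned difference.

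**ICC implied by 1.8.** DE = 1 + (m − 1) × ICC, so ICC = 0.8 / 143 = 0.0056 at m = 144 (0.8 / 179 = 0.0045 at m = 180).

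**Type I error when service is ignored.** If the true variance of the estimated difference in change is DE times what the model assumes, the actual two-sided error is 2 × [1 − Φ(1.96/√DE)]. At DE = 1.8: 1.96/1.342 = 1.461, giving 0.144. By the plan's own factor, 576 clients carry the information of 576 / 1.8 = 320.

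As a check, four services of 144 clients were simulated, with each client's change tested between arms. This is what a client random-intercept model reduces to with balanced data. Rejection under the null was 14.7% at ICC 0.0056 and 4.9% at ICC 0. A t-test on the four service means, on the same simulated data at ICC 0.0056, rejected 4.7%.

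**Inference on four services.** Degrees of freedom are 4 − 2 = 2, and t(0.975, 2) = 4.303. At DE = 1.8 the interval widens by 4.303 × √1.8 / 1.96 = 2.9. For power, the standard error in SD units is √(2 × 1.8/288) = 0.1118, the noncentrality is 0.313/0.1118 = 2.80, and the noncentral t on 2 df gives 35%. Reaching 80% needs a noncentrality of 5.65, that is a difference of 5.65 × 0.1118 = 0.63, about twice the planned one.

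**Range.** Every ICC below except 0.0056 is an assumption.

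| ICC of change | DE = 1 + 143 × ICC | Type I error, two-level model | Power on 2 df at planned difference |
|---|---|---|---|
| 0.001 | 1.14 | 6.7% | 48% |
| 0.0056 (from 1.8) | 1.80 | 14.4% | 35% |
| 0.01 | 2.43 | 21% | 28% |
| 0.02 | 3.86 | 32% | 21% |
| 0.05 | 8.15 | 49% | 13% |

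**The case against.** The best defence is that the text is less settled than it looks. Client Outcomes opens by promising multilevel models for the comparison between services, and then mentions methods for clustered data. Its two paragraphs list different covariates (locality, socio-economic status and nurse contacts appear only in the first), so the second may be illustrative. The article is also condensed, and a fuller document could name a service level. This leaves some ambiguity but does not rescue the plan. The mention of clustered data is tied to client confounders and names no cluster, while the next paragraph numbers the levels and names the decisive test. That is a specification that leaves service out, not a detail left for later.

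Three stronger readings are tempting, and the documents do not support them.

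- A reader might infer that all service drift is counted as an intervention effect and that a better model would remove it. Only the difference between the two arm averages enters the estimate, and it stays there under a service-level analysis too. That is a limit of the 2-versus-2 design. The fault in the analysis is understated uncertainty.
- A reader might take error rates of 21% to 49% as the expected size. They rest on ICCs above the 0.0056 implied by 1.8. Nothing in the documents supports those values over a smaller one, and at 0.001 the error is 6.7%.
- A reader might say that the model treats four units as 576 independent ones. That figure is the expected number of completers; a model that accepts unbalanced data could use up to 720 clients, and it does handle correlation within a client.

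**Conclusion.** The point stands as an error in the plan as written: the model for the client outcomes omits the randomised unit and conflicts with the protocol's own allowance for clustering. Unless services do not differ at all in change over time, the interaction test is anti-conservative.

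The only size anchored in the protocol is about 14% type I error against a nominal 5%. It assumes that the 1.8 refers to services (the cluster is not named) and that it applies to change rather than to a single measurement. It also assumes a two-sided test, 144 completers in each service and a continuous outcome. Departures from these assumptions alter the size of the error. The direction is not in doubt.

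**What to change.** Make the primary inference for client outcomes account for service, in one of two ways:

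1. Compute a covariate-adjusted mean change per service and compare 2 versus 2 with a t-test on 2 df (critical value 4.30).
2. Add service as level 3 with a random service-by-time effect and small-sample degrees of freedom. A random intercept for service alone is not enough, because it leaves variation in change untouched. With four services this variance will be poorly estimated.

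Report the two-level model only as a labelled sensitivity analysis. State as a limitation that service drift remains in the point estimate.

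The change needs no new data, but it is not free. At design effect 1.8, 95% intervals become about 2.9 times wider and power at the planned differences falls to about 35%. Power and Sample Size Calculation should therefore restate its 80%, and conclusions should rest on estimates and intervals rather than on significance. A permutation test offers no way round this: with unrestricted 2-versus-2 allocation there are six arrangements, so the smallest two-sided p-value is 2/6 = 0.33.

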### Study Aim, Objectives and Hypotheses

The overall aim of this study is to evaluate the impact of a brief lifestyle intervention delivered by GCNs in routine practice on changes in clients' SNAP risk factors.

The study has three main objectives:

1. To develop an intervention to facilitate GCNs to undertake lifestyle screening and brief intervention during routine consultations and to promote referral of 'at-risk' clients to available private and public services;

2. To evaluate the impact of these interventions on change in clients' lifestyle risk factors and related mediators (eg stages of change);

3. To describe the indicative costs and resources utilised by the community nurse services in delivering the intervention.

It is hypothesised that:

1. 20% more clients who are at high risk (defined as having at least one lifestyle risk factor) in the intervention group will be offered evidence-based interventions to modify their risk factors compared with clients in the comparison group.

2. Clients in the intervention group will be significantly more likely to progress in their stage of change compared to comparison clients.

3. Clients in the intervention group will have a reduction in their lifestyle risk factor scores compared to clients in the comparison group.

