***Intermediate outcomes (mediator variables)***		

Progression in stages of change (number and % high clients in each stage of change) as measured by five point intention scales [34]	Client telephone survey	Baseline, 3 and 6 months

Change in nurse self reported confidence and attitude scores for SNAP management measured by nurse survey.	Clinician survey	Baseline, 6 and 12 months

Changes in clients' lifestyle risk factors is self reported and captured through a 15 minute telephone survey conducted with clients at baseline (prior to first nurse visit), three and six months. The telephone survey is being conducted by trained independent data collectors blinded to the group allocation (intervention or comparison) of services. Measures of lifestyle risk factors used in the survey are based on validated tools as detailed in Table 4. Nurse outcomes are being measured using a web-based survey adapted from the Preventive Medicine Attitudes and Activities Questionnaire (PMAAQ) [38] administered at baseline, six and 12 months. All data collection tools have been piloted prior to use.

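### One linear 0/1/2 time term cannot separate the short- and medium-term effects: it ties the 3-month effect to half the 6-month effect and understates or misses an early or fading one

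*Protocol article*

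**What the plan says.** The Client Outcomes part of Statistical Analysis lists the independent variables of the multilevel model. Time enters as "time (0 = baseline, 1 = three months & 2 = six months) as a continuous variable". The model is meant to "test for a significant interaction between time and intervention, which would indicate an effect of the intervention on outcomes". The same section has "multilevel logistic models used for binary responses". It describes no visit-specific contrast and no categorical time term.

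Study Design and Setting says data are collected at "baseline, three months and six months to examine short and medium term change in SNAP risk factors".

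Hypothesis 1 is about offers of help with risk factors, relative to the comparison group: "20% more clients who are at high risk (defined as having at least one lifestyle risk factor) in the intervention group will be offered". It does not say whether the 20% is absolute or relative. Table 4 lists this outcome as primary, measured at all three time points. The text after Table 4 says the client survey is "conducted with clients at baseline (prior to first nurse visit), three and six months".

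**The concern.** The design sets out to look at two horizons, but the stated model has one effect parameter. With a single straight line through 0, 1 and 2, the 3-month effect is not estimated: it is fixed by assumption at half the 6-month effect. The intervention is brief and given over two or more visits, so a gain that comes early and then levels off or fades is a pattern worth guarding against. Under such a pattern the reported interaction would understate the short-term effect or miss it, and a reader would have no 3-month result to set against it.

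Hypothesis 1 raises a related difficulty. It is about the share of clients offered intervention, and the baseline survey comes before any nurse visit, so the baseline value cannot reflect offers made in the trial. A log-odds slope anchored on that baseline is not the between-group percentage difference that the hypothesis names.

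**Working it through.** **Inputs.** From the protocol article: time codes 0, 1, 2; 288 clients per group after 20% loss; design effect 1.8; 5% significance (two-sided assumed); 80% power. Assumed, because the article does not give them: within-client correlation rho 0.5 to 0.7, the dropout pattern, and offer rates. No SD is stated, so the 720 cannot be reproduced. Only the attrition step can: 720 × 0.8 = 576, or 288 per group.

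**Scale.** Effective n = 288/1.8 = 160 per group. The standardised effect with 80% power is (1.960 + 0.842) × √(2/160) = 0.313. This only sets the scale; it does not verify the sample size.

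**Slope weights.** With complete data the slope weight at each time is (t − 1)/Σ(t − 1)², that is −0.5, 0, +0.5. Generalised least squares gave the same weights under exchangeable and AR(1) correlation at rho 0.5 and 0.7. The interaction is therefore half the group difference in baseline-to-6-month change. In units of a full effect at (3, 6 months):
- true (1, 1) is fitted as (0.5, 1);
- true (1, 0.5) is fitted as (0.25, 0.5);
- true (1, 0) is fitted as (0, 0).

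**With attrition.** If 10% are lost before 3 months and a further 10% before 6 months, the 3-month weight rises to 0.03–0.05. A 3-month-only effect is then fitted as 0.03–0.05 at 3 months and 0.07–0.09 at 6 months.

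**Power, complete data, exchangeable rho = 0.5.** The variance of the group difference in 6-month change is (2/160) × 2(1 − 0.5) = 0.0125, so SE = 0.112 and z = 0.313/0.112 = 2.80, giving 0.80. For a half effect at 6 months z = 1.40, giving 0.29. For the 2-df test, the covariance of the two changes is (2/160) × [[1, 0.5], [0.5, 1]]. The non-centrality is 0.313²/0.0125 = 7.85 for patterns (1, 0.5) and (0.5, 1), and 7.85 × 1.333 = 10.46 for (1, 1) and (1, 0).

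| True effect (3, 6 months) | Trend test | 2-df test | 3-month contrast | 6-month contrast |
|---|---|---|---|---|
| Linear growth (0.5, 1) | 0.80 | 0.71 | 0.29 | 0.80 |
| Sustained (1, 1) | 0.80 | 0.83 | 0.80 | 0.80 |
| Fading (1, 0.5) | 0.29 | 0.71 | 0.80 | 0.29 |
| 3 months only (1, 0) | 0.05 | 0.83 | 0.80 | 0.05 |

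With exchangeable rho = 0.7 and the same effect size, trend v 2-df is 0.95 v 0.91, 0.95 v 0.97, 0.44 v 0.91 and 0.05 v 0.97, in the same row order.

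**Offered-intervention outcome.** A logistic model with linear time by group was fitted to assumed proportions (working independence, 160 effective per group):
- 20% at baseline in both groups, then 20% v 40% at both follow-ups. The fitted differences are 3.6, 12.8 and 23.6 points at baseline, 3 and 6 months, where the truth is 0, 20 and 20. Interaction z = 2.47, power about 0.69, against 0.98 for a direct comparison at one visit.
- 5% at baseline, then 30% v 50% at both follow-ups. Interaction z = 1.52, power about 0.33, against 0.96.
- 20% at baseline, then 20% v 40% at 3 months and 20% v 20% at 6 months. Interaction z = 0.

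**The case against.** Gradual change is also plausible here. The article stresses contact over an extended period, referral for more intensive help, and staged progress towards change. If growth is linear, the planned trend test beats the 2-df test (0.80 v 0.71). If the effect is sustained, the two are close. This stands: the early-or-fading pattern is a risk, not an established fact.

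Three stronger readings are tempting, and the documents support none of them.

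- A reader might infer that the plan ignores the 3-month data. That holds only for the linear-model point estimate with complete data. The article expects 20% loss, under which the 3-month means gain a small weight, and those data feed the variance estimate in any case.
- A reader might infer that Hypothesis 1 cannot be properly tested. The interaction is still a valid test of no differential change. The section introduces these models for change in lifestyle risk factors, so it is not explicit that the offered outcome is tested only this way. Nor does the hypothesis restrict offers to community nurses: clients getting lifestyle help from their GP are not excluded, so the baseline offer rate need not be near zero. The power loss depends heavily on that rate. Ignoring clustering, with 288 per group and 40% v 20% at follow-up, simulated interaction power was 37–45% for a 1% baseline rate but about 92–99% for a 20% rate.
- A reader might infer that a 6-month contrast is more precise than the slope. With complete, exchangeable data it is simply twice the slope, with variance factor 2(1 − rho) either way: 1.00 at rho 0.5 and 0.60 at rho 0.7. A variance 1.7 to 2.0 times smaller belongs to a different analysis, the baseline-adjusted mean of both follow-ups, (1 + rho)/2 − rho²: 0.36 at rho 0.7 and 0.50 at rho 0.5.

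**Conclusion.** The point holds as a mismatch between the stated model and the stated purpose of the two follow-ups. The half-effect constraint is exact. The zero weight on the 3-month means is exact for the linear model with complete data under the correlation structures tried, and nearly so under the attrition pattern tried. The cost is large if the effect fades (0.29 v 0.71) or is gone by 6 months (0.05, the nominal error rate, v 0.83). It is negligible if the effect is sustained (0.80 v 0.83), and reversed if growth is linear. These powers rest on an assumed within-client correlation of 0.5, complete data, the article's design effect taken at face value, and an effect size scaled to 80% power.

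The sample size is not undermined for a continuous outcome whose full effect is present at 6 months, since the trend test then has the power of a 6-month contrast. For the offered outcome the conclusion is conditional: if the stated logistic model is used, its slope does not estimate the difference in Hypothesis 1. How much power that costs cannot be fixed from the document, because no baseline offer rate is given.

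**What to change.** Enter time as a three-level factor with group-by-3-month and group-by-6-month terms. Name one primary contrast in advance, for example 6 months, and report the other as secondary. If 6 months is primary, an effect confined to 3 months will still give a null primary result; the gain is that the short-term effect is estimated and visible rather than assumed.

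For the offered-intervention outcome, compare the follow-up proportions between groups as a risk difference with an interval that allows for clustering, and say whether the hypothesised 20% is absolute or relative.

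The cost is analysis wording, one extra parameter per outcome, and some loss of joint-test power if change is truly linear (0.71 v 0.80 in the illustration). No new data are needed.

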#### Recruitment of Clients

In order to reach the required sample size, GCN services are required to recruit 180 clients each. Clients referred to participating GCN services meeting the selection criteria (Table 2) are invited to participate in the study. Potential participants are contacted by phone on the day of referral (where ever possible) by a trained local recruitment officer. Clients who consent to take part in the study then participate in a telephone interview to collect baseline data (see data collection). A total of 720 clients (average 180 clients per service) will be recruited at baseline. We expect a 20% loss to follow-up of clients of over the study period, leaving 576 clients (or 288 in each group).

**Table 2 T2:** Selection criteria for recruiting clients to participate in the trial

Types	Selection criteria
**Inclusion criteria**	Clients referred to community nursing services Age 30-80 years Able to read and understand English at a level that enables the client to participate in a telephone administered survey and to understand the participant information sheet.

**Exclusion criteria**	Palliative care clients Clients receiving one off visit or service Clients with significant cognitive impairment (unable to complete telephone administer survey). Clients who are currently receiving help in changing their lifestyle from a health professional (other than their GP) such as a dietitian or exercise physiologist Clients who are currently attending a chronic disease management program such as cardiac rehabilitation, diabetes education program etc. Clients who have attended the generalist community nursing service in the previous six months (and therefore may have already received lifestyle intervention)

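### For the four continuous primary outcomes, the tested group-by-time term is a raw difference in change that the planned covariates do not adjust; a model conditioning on the baseline value would be more precise

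*Protocol article*

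**What the plan says.** The section Statistical Analysis, Client Outcomes, fixes the structure: "In the study we will use multilevel models in which three repeated measures (the level 1 units) are nested within clients (level 2 units"). The listed terms are intervention, time as a linear score (0, 1, 2), sex, age, health status and intervention by time. The effect test is the interaction: "This model will allow us to test for a significant interaction between time and intervention, which would indicate an effect of the intervention on outcomes".

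The same section states the purpose of the covariates: "Co-variates will be included in the analysis to adjust for baseline differences between the intervention and control groups". Those it names are client characteristics and number of nurse contacts. The baseline value of the outcome is not among them, and nothing constrains the groups to a common baseline mean.

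The text under Table 4 says the outcomes come from a "15 minute telephone survey conducted with clients at baseline (prior to first nurse visit), three and six months". The baseline value therefore precedes any nurse contact and is a legitimate covariate already in hand.

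On size, the section Power and Sample Size Calculation says: "A sample size of 360 clients in each group (total n = 720) is required to have 80% of power". It adds: "This is based on 5% significance level and 80% power (β = 0.8 and α = 0.05) allowing 20% lost to follow-up". Clustering is allowed for by an inflation factor of 1.8. The section and Table 4 frame the continuous primary outcomes as change. No SD and no correlation between baseline and follow-up is given.

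**The concern.** The stated aim and the stated model do not meet. The covariates are there to deal with baseline differences, but all those in the listed model are fixed over time within a client and enter as main effects. In a model whose test is a group-by-time term, such main effects absorb differences in level and leave the contrast in change alone. The variable likely to predict follow-up best, the client's own earlier value, is subtracted with a coefficient of 1 instead of being given its estimated coefficient.

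Two things follow for the continuous outcomes. The contrast has more variance than a baseline-adjusted one whenever rho is below 1. And if the groups happen to start apart by chance, part of that gap closes by itself and is counted in the interaction. These are two views of one loss: averaged over chance gaps, the second effect is the extra variance in the first.

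**Working it through.** **Inputs from the protocol.** 360 clients per group, 20% loss, design effect 1.8, 5% significance (two-sided assumed), 80% power. **Assumed, because not given:** SD and rho.

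**1. The plan's own figures.** 360 × 0.8 = 288 per group retained, as stated under Recruitment of Clients. Effective size is 288/1.8 = 160 per group. The detectable effect is (1.960 + 0.842) × sqrt(2/160) = 0.313 SD. Working forward from 0.313 SD gives 161 per group, and 161 × 1.8/0.8 = 362, close to 360. This is only a consistency check, since the SD was solved from the stated sample size.

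**2. What the interaction estimates.** With complete data and a client random intercept, the generalised least squares weights for the slope on (baseline, 3 months, 6 months) are (-0.5, 0, 0.5) at rho 0.3, 0.6 and 0.9. Twice the interaction is then the difference in mean change from baseline to six months. In a simulated trial of 288 per group, twice the fitted interaction was 0.2546 with and without age and sex, and the raw difference in change was also 0.2546. In a second simulated trial, with a prognostic age covariate imbalanced by 0.5 SD, the interaction was 0.1367 with and without age, sex and health status. With 20% of six-month values missing it moved only from 0.1213 to 0.1215.

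**3. Precision if the same rho holds for clients and services.** Variance is proportional to 2(1 - rho) for change and 1 - rho² for the adjusted contrast, so the ratio is (1 + rho)/2. If change has 80% power, adjusted power is Φ(2.80/sqrt(ratio) - 1.96):

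- rho 0.5: ratio 0.75, power 90%
- rho 0.7: ratio 0.85, power 86%
- rho 0.9: ratio 0.95, power 82%

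**4. Precision if service differences fully persist.** A design effect of 1.8 splits the variance of a group difference into a client part, 1, and a service part, 0.8. Service effects cancel in change. In the adjusted contrast a share (1 - rho) of each remains. The ratio is [(1 - rho²) + 0.8(1 - rho)²] / [2(1 - rho)] = 0.9 + 0.1 rho. Scaled from 80% as before:

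- rho 0.5: ratio 0.95, power 82%
- rho 0.7: ratio 0.97, power 81%

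The ratio runs from 0.93 at rho 0.3 to 0.99 at rho 0.9. It stays below 1, so the gain shrinks but does not reverse.

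**5. Effect of a baseline gap d.** If d is chance, the expected follow-up gap is rho × d. The change contrast is off by (1 - rho)d in size and the adjusted contrast by about zero. If d is lasting, the change contrast is about right and the adjusted one is off by (1 - rho)d. At rho 0.5:

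- Client-level chance gap of one standard error: sqrt(2/288) = 0.083 SD. Shift in the change estimate: 0.5 × 0.083 = 0.042 SD, and 0.042/0.313 = 13% of the detectable effect.
- Service-level gap of one standard error: sqrt(2 × 0.8/288) = 0.075 SD. If lasting, shift in the adjusted estimate: 0.5 × 0.075 = 0.037 SD, or 12%.

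Simulation with a gap of 0.1 SD at rho 0.5 agrees. A chance gap moved change by -16% of the target effect and the adjusted estimate by about 0. A lasting gap moved change by about 1% and the adjusted estimate by +17%.

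**The case against.** The best defence is that the plan chose an estimator to suit its design. It calls the study quasi-experimental, allocates four services two against two, and names locality and socio-economic status as confounders. Where groups differ lastingly, a difference in change is a standard choice and conditioning on baseline is the one that errs. Step 5 shows the two risks are nearly mirror images. This part stands, and is why both analyses should be reported.

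It also stands that no shortfall against the stated power is shown. If the SD behind the sample size was that of change, the 80% holds and only extra precision is forgone. Dropping clients with no follow-up is a real cost too, since the plan chose multilevel models partly to accommodate attrition.

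The defence does not remove the point. Services were randomly allocated, which supports conditioning on a value measured beforehand. The protocol does not argue that gaps will last. Even with fully persistent service effects the adjusted contrast is no less precise. And the promised covariate adjustment still does not reach the tested term.

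**Conclusion.** The point holds for the four continuous primary outcomes: the tested term is a raw difference in change, and the listed covariates leave it as it is (exactly so with complete data, very nearly with missing values). The gain from adjusting runs from 1 or 2 power points (lasting service differences) to about 10 at rho 0.5 or 6 at rho 0.7 (same rho at service level), given 80% power for the change analysis. It is close to nil for weight if its rho is very high.

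A reader might infer more than the documents support:

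- That adjustment would bring power to about 90% outright. This needs rho near 0.5 and the same rho at service level; neither is given.
- That the planned estimate is inherently biased by regression to the mean. Table 2 does not select clients on a high baseline value, so the shift arises only from a chance gap.
- That the full one-standard-error gap with the design effect (0.112 SD, an 18% shift at rho 0.5) regresses. Of its variance, 0.8/1.8 = 44% lies between services and need not regress; the client-level figure is 13%.
- That every primary outcome is affected. The binary outcome, whether high-risk clients were offered intervention, falls under a logistic model and is not covered.

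**What to change.** For each of the four continuous primary outcomes, model the three- and six-month values as responses, with the client's own baseline value of that outcome (interacting with visit), group, visit and group by visit. Report the adjusted six-month group difference as the effect. Keep the planned interaction model as a named sensitivity analysis, report both, and say that a lasting gap between services would favour the planned model. Name the primary analysis before results are seen.

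A service-mean baseline covariate is not a workable guard against lasting gaps. With four services, after the intercept, group and that mean, 4 - 3 = 1 service-level degree of freedom remains.

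The change is to analysis wording only, with no new data, visits or clients. The costs are that clients with neither follow-up survey leave the adjusted model, though they carry little information on change in the planned one, and that the two estimates may differ and need explaining.
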